## Abstract

**Background::**

Insomnia is a common, recurrent, and tenacious sleep problem, especially the chronic insomnia. Repetitive transcranial magnetic stimulation (rTMS) at right dorsolateral prefrontal cortex (r-DLPFC) is used in chronic insomnia, and repetitive magnetic stimulation (rMS) at Shenmen (HT7) acupoint may be an alternative approach. However, the efficacy and mechanism of rMS at HT7 acupoint for chronic insomnia has not been confirmed.

**Methods/design::**

This is a 3-armed randomized positive-controlled noninferiority clinical trial. We will allocate 45 subjects aged between 18 and 65 years old, diagnosed with initial chronic insomnia over 3 months to 3 groups randomly in a ratio of 1:1:1. Patients in the experimental group will be treated with rMS at HT7 acupoint while the others in the control group will be treated with rTMS at r-DLPFC or waiting treatment. All will be given rMS at HT7 or rTMS at r-DLPFC or no treatment for 10 days, and then received 20-day follow-up. Patients will be evaluated with the insomnia severity index and Pittsburgh sleep quality index for sleep state, Beck Depression Inventory-2nd edition scores for the depression state, Beck anxiety inventory scores for the anxiety state, and Montreal Cognitive Assessment scores for the cognition state before and the 10th day of treatment, 30th day of follow-up; study on mechanisms of rMS will be revealed through the resting motor threshold diversity of the motor cortex before and the 10th day of treatment, 30th day of follow-up. Baseline characteristics of patients will be summarized by groups and compared with Chi-squared for categorical variables, and analysis of variance or Kruskal–Wallis test for the continuous variables. Primary and secondary outcomes according to the measurement times are applicable to univariate repetitive measurement deviation analysis or analysis of variance, or Kruskal–Wallis test.

**Conclusion::**

The present study is designed to preliminarily investigate short-term efficacy and mechanism of rMS at HT7 acupoint therapy on chronic insomnia, also to explore the correlation between motor cortex excitability and chronic insomnia. With this research, we are looking forward to find out an appropriate alternative and easy therapy for chronic insomnia individuals compared with rTMS at r-DLPFC.

**Trial Registration::**

The trial was registered on Chinese Clinical Trial Registry (http://www.chictr.org.cn/index.aspx) with the ID ChiCTR1900026844 on October 24, 2019.

## Introduction

1

Insomnia is a common, recurrent and tenacious sleep problem, adults incidence in the range of 10% to 15%, especially the chronic insomnia (CI).^[1]^ CI has been regarded as an independent risk factor for coronary heart disease, acute myocardial infarction, heart failure, hypertension, diabetes, depression, dementia, and other chronic diseases. Besides, it may cause daytime fatigue, cognitive impairments (attention, memory, executive ability), negative emotions, and affect the individuals quality of life.^[2–7]^ It indicates that hyperarousal is one of the main pathologic mechanisms of CI.^[8]^

The short-term efficacy of sleep agents has been proved, but they often lead to a series of side effects, like daytime dysfunction, sleep driving, abnormal behavior, and depression deterioration. Moreover, it does exist addiction, which might make patients resistance and low compliance for long-term users.^[9,10]^ Due to the lack of cultural background and diplomats in China, the implementation of cognitive behavioral therapy in basic hospitals and general hospitals is rarely used at present. Thus, it is essential to select an effective, safe, no side effects, and no addiction sleep method. Repetitive transcranial magnetic stimulation (rTMS) is a noninvasive neuroregulatory technique in line with the above characteristics, which has been widely used in clinic by reducing cortical excitability in CI patients.^[11]^ Low-frequency (1 Hz) rTMS at bilateral frontal or parieooccipital regions is recommended for sleep disorders in the *Chinese experts consensus on rTMS* (level of evidence: level II/III).^[12]^ However, the rTMS for patients with intracranial metal implants, stents, glaucoma, and hypertension is limited. In traditional Chinese medicine (TCM), insomnia is an appropriate disease in the acupuncture spectrum of diseases. *Shenmen* acupoint (HT7) is the *yuan* acupoint of Heart-Channel, the most frequently selected for insomnia.^[13]^ Acupuncture at HT7 acupoint can activate related brain regions highly associated with improving sleep, emotional, and cognition.^[14,15]^ Thus, the problem of acupuncture therapy is that its manipulations are difficult to replicate, and some patients cannot tolerate repeated pain stimulation. Studies have shown that the effects of repetitive magnetic stimulation (rMS) at acupoints can be quantified, similar to acupuncture effect,^[16]^ noninvasive and painless. In particular, low frequency (1 Hz) rMS at HT7 acupoint can make brain activity in good order and reduce brain excitability for the healthy.^[17]^ Furthermore, low frequency (1 Hz) rMS at HT7, PC6 and SP6 can be also good for the subhealth insomnia ones in enhancing interaction between brain regions, increasing transmission speed and efficiency between brain networks, and improving brain cognitive function.^[18]^ However, there are few clinical studies on low frequency (1 Hz) rMS at HT7 acupoint for CI.

However, compared with rTMS at right dorsolateral prefrontal cortex (r-DLPFC), no sufficient clinical trial data and solid evidence could confirm whether acupoint could yield certain efficiency in treating CI and how it works. It is necessary to verify the effectiveness and mechanism of rMS at acupoint on the sleep quality and cortical excitability from senior quality studies. Now, the evidence about low-frequency rMS at HT7 acupoint for CI is inadequate and must apply further strictly design clinical studies.

The primary objectives of this study are to evaluate the short-term efficacy and mechanism of rMS at HT7 acupoint and follow-up on CI preliminarily.

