### Study design

2.1

This is a single-center, randomized, positive-controlled, noninferiority clinical pilot trial. A total of 54 participants will be randomized into 3 groups at a ratio of 1:1:1. Participants in the treatment group will be treated with rMS at HT7 acupoint. Participants in the control group will be treated with rTMS at r-DLPFC or waiting treatment.

The whole study period is 35 days, including 5-day baseline observation, 10-day treatment, and 20-days follow-up. Subjects will be evaluated with scales for clinical efficacy before and the 10th day of treatment, 30th day of follow-up, and monitored by rMS/rTMS for therapeutic mechanism before and the 10th day of treatment, 30th day of follow-up (Fig. 1).

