#### Exclusion criteria

2.3.2

1.Subjects, diagnosed with secondary insomnia, such as mental disorders (depression, anxiety, schizophrenia, diphasic, etc) or physical diseases (pain, stroke, coronary heart disease, tumor, etc) or other nonpathologic factors (poor sleep hygiene, jet lag, shift work, etc);2.With severe depression and anxiety (PHQ-9 scores ≥20 points; GAD-7 scores ≥19 points),^[22]^ high risk of sleep apnea (>3 items in the Stop Bang questionnaire), aphasia and severe cognitive dysfunction (MMSE scores <17 points)^[23]^;3.With severe heart disease, malignancy, kidney, and liver function insufficiency;4.Dependence or abuse of alcohol or drugs;5.With metal foreign bodies (cochlear implant, built-in pulse generator, aneurysm clip, stent, etc) at the treatment sites within 30 cm depth under the skin;6.Participation in any other clinical trial or taking benzodiazepines in recent 2 weeks or receiving TMS, transcranial direct current stimulation, electroconvulsivetherapy, acupuncture and other treatments regularly over the last 1 month;7.Pregnant or lactating women.

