### Study group

2.5

Forty-five participants who meet the criteria with informed consents will be selected. The subjects will be randomly divided into 3 groups in a 1:1:1 ratio, namely the experimental group, positive-control group and waiting list control group, 15 cases in each group.

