##### rMS at HT7 acupoint

2.7.1.1

The rTMS therapeutic apparatus (CCY-II model; Wuhan YiRuiDe Medical Supplies New Technology Co Ltd, Wuhan, China) were used. rTMS is applied to treat CI according to the modern neuro-rehabilitation theory. Acupoint is only left HT7 (*shenmen*) acupoint according to the TCM theory. After preparation, test the resting motor threshold (RMT): the participants will take the sitting position, keep the mood stable and the muscles relaxed. During stimulating M1 region, the coil will be tangent to the scalp, and it will be advisable to adjust the coil to get the maximum amplitude and the best repeatability of motor evoked potential. The stimulus intensity will begin from 30% and gradually increase at a rate of 2.5%. The minimum stimulus intensity (RMT) will be the abdominal contraction in the abductor pollicis brevis muscles of contralateral thumb in 5 out of 10-times consecutive stimuli; locate the stimulus area: the stimulation coil will be placed at the left HT7 acupoint (on the anteromedical aspect of the wrist, radial to the flexor carpi ulnaris tendon, on the palmar wrist crease) (Fig. 2); set the stimulus parameters: the standard mode is selected as the stimulus mode, for instance the frequency as 1 Hz, the total pulses number as 1800, and the intensity as 25% RMT.^[24]^ Start the stimulation after checking the above parameters, and then remove the coil flap after the stimulation. Participants will be treated 2 sessions per day for 10 consecutive days.

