##### rTMS at r-DLPFC

2.7.2.1

Low-frequency (1 Hz) rTMS at r-DLPFC is recommended for sleep disorders in the *Chinese experts consensus on rTMS* (level of evidence: level II/III)^[12]^ and *Guidelines for The Diagnosis and Treatment of Insomnia in China*.^[25]^ After preparation, test RMT: the measurement is same as the experimental group; locate the stimulus area: the stimulation coil will be placed tangent to the scalp on the r-DLPFC (8 cm in front of the midpoint of the connection between 2 ear tips, and then 6 cm toward the right side); set the stimulus parameters: the intensity is selected 100% RMT. Other parameters are same as the experimental group. Participants will be treated 2 sessions per day for 10 consecutive days.

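### The exclusion list covers metal and stents but not glaucoma, hypertension or a seizure history, although the article itself names the first two as limiting rTMS and seizure as an rTMS risk

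*Protocol article*

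**What the plan says.** The Introduction gives a reason for seeking an alternative to cranial stimulation: "the rTMS for patients with intracranial metal implants, stents, glaucoma, and hypertension is limited". That sentence names four conditions.

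Three of the seven numbered items in section 2.3.2 come near them:

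- Item 5 excludes patients "With metal foreign bodies (cochlear implant, built-in pulse generator, aneurysm clip, stent, etc) at the treatment sites within 30 cm depth under the skin".
- Item 3 excludes patients "With severe heart disease, malignancy, kidney, and liver function insufficiency".
- Item 1 excludes patients "diagnosed with secondary insomnia, such as mental disorders", and goes on to physical diseases and to factors such as shift work.

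The positive-control arm receives low-frequency rTMS at the r-DLPFC, where "the intensity is selected 100% RMT" (section 2.7.2.1). The waiting-list arm is untreated for 10 days and then gets the positive-control treatment from day 11 (section 2.7.3).

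On harms, section 2.8 lists epilepsy with headache, scalp discomfort and tinnitus as events likely to be related to rTMS. The Discussion (section 3) gives seizure as a potential risk of rTMS to the head, above all in people with metal implants.

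**The concern.** The article names four conditions as limiting one of its own treatments, and its entry rule deals with two of them. It also names seizure as a possible effect of that treatment without keeping out patients who have already had one. An investigator who applies section 2.3.2 literally would enrol such patients and could then have to give them rTMS at full threshold intensity.

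What is at stake is patient protection at entry. Sample size, error rates and the comparison between arms are not affected, because the entry rule is the same for everyone and is applied before allocation.

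Hypertension at least is foreseeable. The Introduction lists it among the diseases for which chronic insomnia is a risk factor, and the trial admits patients up to age 65. No rate is given, and nothing comparable is said about glaucoma or seizure history.

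**Working it through.** This is a comparison of texts. The plan states no figure on this point that could be reproduced.

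**Step 1: each named condition against the criteria (sections 2.3.1 to 2.3.3).**

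| Condition | Where the article names it | Item that covers it |
|---|---|---|
| Intracranial metal | Introduction | Exclusion 5 |
| Stents | Introduction | Exclusion 5 |
| Glaucoma | Introduction | None |
| Hypertension | Introduction | None by name |
| Epilepsy or seizure | Sections 2.8 and 3, as an effect of rTMS | None as a history |

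**Step 2: could another item catch them indirectly?** Item 1 removes patients whose insomnia is secondary to a disease. Its physical examples are open-ended but include none of the three conditions, and a patient with primary insomnia who also has one of them is outside the item. Item 3 would remove a hypertensive patient who also has severe heart disease or kidney insufficiency, but not one with hypertension alone. So at most some hypertensive patients are caught. The withdrawal criteria refer back to the exclusion criteria and add nothing here.

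**Step 3: which arms are scheduled for r-DLPFC rTMS?** Under 1:1:1 allocation:

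- positive-control arm, from the start of treatment: 1/3
- waiting-list arm, from day 11: 1/3
- together: 1/3 + 1/3 = 2/3

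The article gives two totals. Section 2.1 states "A total of 54 participants will be randomized into 3 groups at a ratio of 1:1:1", and section 2.5 gives 45 in all with "15 cases in each group". The share does not depend on which is right: (15 + 15)/45 = (18 + 18)/54 = 2/3. This is the chance that any one eligible patient is scheduled for cranial rTMS. It does not estimate how many patients have one of the conditions, because the article gives no prevalence.

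**Step 4: do other provisions screen for them?** The step down from 100% to 80% RMT, coil adjustment, medical care and drop-out in section 2.8 all respond to a problem that has already appeared. The licensing and training of physicians in section 2.7 is not an eligibility check. Section 2.12 mentions clinical screening before allocation, but the only printed content of that screening is the criteria checked in Step 1.

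**The case against.** The strongest reply is that the point rests on one undefined word in background text. 'Limited' could mean contraindicated, used with caution, or little studied, and only the first would require exclusion. The sentence serves to motivate acupoint stimulation. Where the Discussion turns to hazards it singles out metal implants, which item 5 covers. Nothing in the article ties glaucoma or hypertension to any adverse effect of rTMS. Relative cautions can be left to clinical judgement, and a condensed article may omit a device checklist or a blood-pressure check that sits in the full protocol.

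Much of this stands. A reader might infer that the protocol knowingly admits patients for whom rTMS is contraindicated, and the text does not support that. A reader might also gauge the problem by counting every patient or session scheduled in the two rTMS arms. Such a count describes the design, since the number of patients who actually have one of these conditions could be zero. Nor do sections 2.8 and 3 say that patients with prior epilepsy are at special risk: they name epilepsy or seizure as an effect. Excluding a history of it is a precaution that follows from that statement, not a correction of a contradiction.

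The appeal to condensation does not remove the point. Section 2.3.2 is a numbered list with specific cut-offs for PHQ-9, GAD-7, Stop Bang and MMSE and a depth limit for metal. It reads as the operative entry rule, and two of the four conditions named in the Introduction are simply absent from it.

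**Conclusion.** The mismatch is real and its weight is low. Of the four conditions that the Introduction says limit rTMS, two reach the exclusion list and two do not. A history of epilepsy or seizure is also not excluded, although seizure is named as an rTMS risk. As printed, a patient with primary insomnia and any of these conditions is eligible and, once randomised, has a two-in-three chance of being scheduled for r-DLPFC rTMS at 100% RMT.

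This rests on two assumptions: that section 2.3.2 is applied as printed, and that no further check exists in a document not shown. No event risk or prevalence is given, so neither harm nor the number affected can be estimated, and no bias in the comparison is claimed. This is a cheap improvement to patient protection, not a defect in the trial's inference.

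**What to change.** Add three exclusions to section 2.3.2:

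1. glaucoma;
2. uncontrolled hypertension, with the blood-pressure limit chosen by the clinicians and written into the criterion;
3. a history of epilepsy or seizure.

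Restricting the second to uncontrolled hypertension fits a caution better than a blanket exclusion would. Screen for all three before randomisation and identically in all three arms, so that eligibility cannot depend on allocation. If the investigators judge that patients with glaucoma or hypertension can safely receive rTMS, they should say so in the protocol and state how these patients will be handled.

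The cost is a short amendment through the ethics route described in section 2.2, a blood-pressure reading, and brief history questions on the screening form. The downside is slightly slower recruitment and a slightly narrower population.

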## Methods/design

2

### Study design

2.1

This is a single-center, randomized, positive-controlled, noninferiority clinical pilot trial. A total of 54 participants will be randomized into 3 groups at a ratio of 1:1:1. Participants in the treatment group will be treated with rMS at HT7 acupoint. Participants in the control group will be treated with rTMS at r-DLPFC or waiting treatment.

The whole study period is 35 days, including 5-day baseline observation, 10-day treatment, and 20-days follow-up. Subjects will be evaluated with scales for clinical efficacy before and the 10th day of treatment, 30th day of follow-up, and monitored by rMS/rTMS for therapeutic mechanism before and the 10th day of treatment, 30th day of follow-up (Fig. 1).

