### Estimation of sample size

2.11

This study is just a pilot study, which designed for efficacy evaluation and mechanism investigation of targeted therapy preliminarily before and after treatment as well as follow-up period. We will plan to enroll a total of 45 participants in this study.

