### Statistical analysis

2.13

Data analysis will be based on intention-to-treat analysis and/or per-protocol analysis principle in the light of data missingness. We will also evaluate the group effect by comparing the analysis results between the above 2 data sets to evaluate robustness of our analytical results.

All data will be analyzed using SPSS23.0 (v23.0; SPSS Inc, Chicago, IL) by 3rd-party statistician. A *P* value <.05 will be considered as significant. Descriptive statistics will be performed with mean, standard deviation, maximum, minimum, and so on by groups and time.

Baseline characteristics of patients will be summarized by groups and compared with Chi-squared for categorical variables, and analysis of variance (ANOVA) (normal distributions) or Kruskal–Wallis test (non-normal distributions) for the continuous variables. Primary and secondary outcomes according to the measurement times are applicable to univariate repetitive measurement deviation analysis or ANOVA or Kruskal–Wallis test. If there is a violation of distribution assumption, appropriate transformation will be used.

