#### Primary outcomes

2.13.1

We will use univariate repetitive measurement deviation analysis with ISI scores and RMT before and the 10th day of treatment, 30th day of follow-up as the outcomes. A significant effect of group indicates that the ISI scores and RMT are different between groups after intervention.

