#### Secondary outcomes

2.13.2

Continuous outcome variables including Pittsburgh sleep quality index scores, Beck Depression Inventory-2nd edition scores, Beck anxiety inventory scores and Montreal Cognitive Assessment scores before and the 10th day of treatment will be analyzed with ANOVA or Kruskal–Wallis test. Categorical outcome variables in the patients’ diary, Chi-squared test will be used for comparison between groups.

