Our protocol is just a pilot study with several limits including the small sample size, open-blinding, and short period of observation time. However, we try our best to attempt to minimize the biases that may influence study results. Finally we intend to demonstrate the hypothesis that rMS at HT7 acupoint as an alternative may be validated for CI.

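### The trial is labelled noninferiority, but its stated primary rule is a three-arm test for a difference at P<.05, which cannot support a noninferiority conclusion

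*Protocol article*

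**What the plan says.** The design label appears twice. The Abstract (Methods/design) states: "This is a 3-armed randomized positive-controlled noninferiority clinical trial". Section 2.1 (Study design) repeats it: "This is a single-center, randomized, positive-controlled, noninferiority clinical pilot trial".

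The analysis is described in sections 2.13 to 2.13.2. The general criterion is that a P "value <.05 will be considered as significant". For the primary outcomes the method is repeated-measures analysis of variance: "We will use univariate repetitive measurement deviation analysis with ISI scores and RMT before and the 10th day of treatment", with day 30 as the last time point. The article then says how the result is to be read: "A significant effect of group indicates that the ISI scores and RMT are different between groups after intervention". The secondary scales are also tested for a difference: "before and the 10th day of treatment will be analyzed with ANOVA or Kruskal–Wallis test".

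Section 2.11 gives a total of 45 on pilot grounds: "This study is just a pilot study, which designed for efficacy evaluation and mechanism investigation". Section 2.5 puts 15 in each arm. Section 2.1 gives a total of 54, which would be 18 per arm. Under section 2.7.3 the waiting-list arm is untreated for 10 days and then receives the r-DLPFC treatment from day 11. The Discussion closes with the aim: "Finally we intend to demonstrate the hypothesis that rMS at HT7 acupoint as an alternative may be validated for CI".

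**The concern.** A noninferiority conclusion needs one particular comparison (HT7 against r-DLPFC), in one direction, judged against a margin. The rule in section 2.13.1 is of another kind. It asks whether any of three groups differ, it has no direction, and it does not single out HT7 against r-DLPFC. A margin-based criterion would have to replace this rule; it could not simply be added as detail.

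What is at stake is the claim made at the end. The stated hypothesis is that HT7 may be validated as an alternative. Under a noninferiority label, two results could be taken as support for it: a significant group effect, which an untreated arm can produce alone, or the absence of a significant difference between the two active arms, which in a small trial is weak evidence of anything.

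**Working it through.** **Plan's own figure.** The only sample-size figure is the total (45, or 15 per arm). It cannot be reproduced, because the article gives no effect, SD, margin or power. Section 2.11 explains this by the pilot status.

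**Inputs.** From the document: three arms at 1:1:1; 15 per arm (18 if the total is 54); alpha 0.05; waiting list untreated to day 10. Assumed: outcomes in SD units with higher meaning worse; a single time point (day 10) in place of the repeated-measures analysis; the true differences and margins named below.

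**1. What a significant result shows.** The noncentrality of the three-arm F test is n × Σ(μᵢ − μ̄)². Order the means as HT7, r-DLPFC, waiting list, with the waiting list 1 SD worse than r-DLPFC.

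- HT7 equals r-DLPFC: means (0, 0, 1), μ̄ = 1/3, sum of squares = 1/9 + 1/9 + 4/9 = 2/3.
- HT7 equals waiting list: means (1, 0, 1), μ̄ = 2/3, sum of squares = 1/9 + 4/9 + 1/9 = 2/3.

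With 15 per arm the noncentrality is 15 × 2/3 = 10 in both cases, on 2 and 42 degrees of freedom. Power is 78.5% in both. A simulation of 40,000 trials gave 78.6% and 78.5%. With 18 per arm the noncentrality is 12 in both cases and power is about 86%. The test is therefore equally likely to be significant when HT7 matches the active control and when it does nothing.

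**2. What a non-significant result shows.** The plan states no pairwise test, so this is the test a reader would have to add in order to compare the two active arms. The standard error is √(2/15) = 0.365 SD. For a true inferiority of 0.5 SD the noncentrality is 0.5/0.365 = 1.37. On 28 degrees of freedom the two-sided power is 0.262, so the inferiority is missed 74% of the time. For 0.75 SD, power is 0.509 and the miss rate is 49%. With 18 per arm the miss rates are 69% and 41%.

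**3. Precision of the pairwise estimate.** The half-width of the two-sided 95% interval is t(0.975, 28) × √(2/15) = 2.048 × 0.365 = 0.75 SD. With 18 per arm it is 2.032 × √(2/18) = 0.68 SD.

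**4. Power if noninferiority were really tested.** With no true difference and one-sided 0.025, the normal approximation is Φ(margin/SE − 1.96). All margins here are assumptions.

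| Margin (SD) | 15 per arm | 18 per arm | n per arm for 80% |
|---|---|---|---|
| 0.3 | 13% | 14% | 175 |
| 0.5 | 28% | 32% | 63 |
| 0.75 | 54% | 61% | 28 |
| 1.0 | 78% | 85% | 16 |

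For 15 per arm and 0.5 SD: 0.5/0.365 − 1.96 = −0.59, and Φ(−0.59) = 0.28. Using the t distribution lowers the 15-per-arm figures slightly, to 26% at 0.5 SD and 51% at 0.75 SD.

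**The case against.** Much of the opposing case stands, and it limits the point.

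- **Unseen documents.** A margin, a confidence-interval criterion and pairwise contrasts are often left to a full protocol or SAP. A reader might infer that no margin exists. The article does not establish that, and the absence is not the finding. The finding is that the rule on the page is the wrong type for the design on the page.
- **Pilot purpose.** The primary objective in the Introduction is preliminary efficacy and mechanism, and noninferiority is not mentioned there. The small sample is acknowledged. An omnibus test with a waiting list can serve that objective, and a missing power calculation is no separate defect. This supports removing the label; it does not reconcile label and rule.
- **No stated misuse.** A reader might infer that the plan equates non-significance with noninferiority. It does not say so: section 2.13.1 interprets only a significant result, and the Discussion is hedged.
- **Size.** A reader might infer that a non-significant result is to be expected even when HT7 is clearly worse. The numbers do not support this. The 74% and 49% belong to a pairwise test that the plan does not state, and 49% is under half. For the three-arm test with the waiting list 1 SD worse than r-DLPFC, significance occurs in about 65% of trials if HT7 is 0.5 SD worse and 69% if it is 0.75 SD worse. Non-significance is usual only if r-DLPFC's own benefit is small (26% significant when both other arms are 0.5 SD worse).
- **Simplification.** The equal-power result is for day 10 alone. A repeated-measures group effect also uses baseline and day 30, when the waiting list has had r-DLPFC treatment, so 78.5% does not carry over exactly. The lack of direction and of a named contrast does.

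**Conclusion.** The contradiction holds. The Abstract and section 2.1 declare noninferiority against r-DLPFC, while sections 2.13 and 2.13.1 set a test for any difference among three arms. No result of that test, significant or not, can support noninferiority. This is certain from the text and needs no assumption.

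The sizes do rest on assumptions: SD units, a single time point and, for the 78.5%, a 1 SD benefit of r-DLPFC over waiting list. The half-width of about 0.75 SD (0.68 SD with 18 per arm) depends only on the arm size and an unadjusted comparison. The conflict between 45 and 54 participants does not alter the conclusion.

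**What to change.** **Recommended.** Remove the noninferiority label from the Abstract and section 2.1 and describe the trial as a pilot. State in section 2.13.1, and reflect in the closing sentence of the Discussion, that neither a significant omnibus result nor a non-significant difference validates HT7 as an alternative to r-DLPFC. Add the HT7 minus r-DLPFC difference in ISI at day 10 with a two-sided 95% confidence interval, preferably baseline-adjusted, as the pairwise estimate. Day 10 precedes the waiting-list arm's treatment, so all three arms can still be compared there as randomized. Leave the RMT and day-30 outcomes in place as stated.

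**If the sponsor keeps the label.** Fix and justify an ISI margin before any outcome data are seen, and conclude only from the confidence limit for HT7 minus r-DLPFC against it. Disclose that power with 15 per arm is low: about 28% at an assumed 0.5 SD margin and 54% at 0.75 SD.

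**Cost.** The recommended route changes wording and adds one estimate, with no extra patients or visits; the price is a more modest claim. Keeping the label is not a wording change alone if noninferiority is to be tested with usual power: at an assumed 0.5 SD margin, 80% power needs about 63 per arm.

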### Randomization

2.12

After recruitment, the patients who meet the eligibility criteria would be randomly and equally divided into 3 groups at a ratio of 1:1:1 with random number table method. Each subject will be registered with a unique ID. After the clinical screening and getting the informed consent forms, subjects will be assigned to experimental group (rTMS at HT7), positive-control group (rTMS at r-DLPFC), and waiting-list control group (no treatment) randomly. Each subject will receive the different stimulation forms, even no stimulating, whereas all subjects will be aware of the grouping.

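### Section 2.1 randomises 54 participants, but the abstract, section 2.5 and the sample size section 2.11 say 45 (15 per arm)

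*Protocol article*

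**What the plan says.** Four places in the protocol article give the size of the trial.

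- Section 2.1 (Study design): "A total of 54 participants will be randomized into 3 groups at a ratio of 1:1:1". No group size is given there.
- Abstract, Methods/design: "We will allocate 45 subjects aged between 18 and 65 years old", in three groups at 1:1:1.
- Section 2.5 (Study group): "Forty-five participants who meet the criteria with informed consents will be selected". They are then divided at random, "namely the experimental group, positive-control group and waiting list control group, 15 cases in each group".
- Section 2.11 (Estimation of sample size): "We will plan to enroll a total of 45 participants in this study".

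Section 2.11 gives the basis for the number as "This study is just a pilot study, which designed for efficacy evaluation and mechanism investigation of targeted therapy preliminarily". It states no effect size, standard deviation, margin, power or expected loss. Section 2.12 (Randomization) repeats the equal allocation without a total: "randomly and equally divided into 3 groups at a ratio of 1:1:1 with random number table method".

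**The concern.** The number to be randomised is a basic design quantity, and the article gives two values for it. Three things follow from that number: how many entries the allocation list holds, when recruitment is complete, and how many participants form the denominator of the intention-to-treat analysis named in section 2.13. A reader of section 2.1 alone would expect 54 in each of these roles. A reader of section 2.5 or 2.11 would expect 45. When results are reported, a trial that stopped at 45 would look 9 short against section 2.1, and one that reached 54 would look 9 over against the other three places.

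**Working it through.** **Inputs.** Totals of 54 (section 2.1) and 45 (abstract, sections 2.5 and 2.11); allocation 1:1:1 (sections 2.1, 2.5 and 2.12); 15 per arm (section 2.5); significance level from section 2.13, "A *P* value <.05 will be considered as significant", with sidedness not stated.

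**The plan's own figures.** Neither total can be derived from a power formula, because the article supplies no inputs for one. The per-arm figure can be checked:

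- 45 / 3 = 15, which agrees with section 2.5.
- 54 / 3 = 18, a number that appears nowhere in the article.

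**Size of the discrepancy.** 54 − 45 = 9 participants, or 3 per arm; 9 / 45 = 20%.

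**Could 45 be what remains of 54 after losses?** The loss rates that would connect the two figures are:

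| Method | Calculation | Loss rate needed |
|---|---|---|
| Divide the total by (1 − d) | 1 − 45/54 | 16.7% |
| Multiply the total by (1 + d) | 45 × 1.20 = 54 | 20% |
| Inflate each arm and round up | 15 / 0.85 = 17.6, so 18; 3 × 18 = 54 | 15% |

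Dividing by (1 − d) at 20% gives 45 / 0.80 = 56.25, rounded up to 57, not 54. So the arithmetic permits a link at some rates, but no rate is stated in the article. The wording also does not fit: 45 is the number allocated in the abstract, the number selected and then divided in section 2.5, and the number enrolled in section 2.11. It is never described as the number completing or evaluable.

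**Effect on precision.** Assume a two-sided 95% interval for the difference between two arm means, a common SD, n per arm, and no losses. The half-width in SD units is t(0.975, 2n − 2) × √(2/n).

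- n = 15: t(0.975, 28) × √(2/15) = 0.748 SD
- n = 18: t(0.975, 34) × √(2/18) = 0.677 SD

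The difference is 0.748 − 0.677 = 0.071 SD. With 1.96 in place of t, the values are 0.72 and 0.65 SD, so the comparison does not depend on the approximation.

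**The case against.** The best defence is that this is a slip with an obvious answer. 45 appears three times, once spelled out in words and once in the section whose purpose is to set the size. The only explicit group size, 15, agrees with it and is not itself contradicted, since 18 arises only by division. 54 occurs once and is 45 with its digits reversed. The trial is called a pilot and claims no power, so no stated power or margin is invalidated, and the outcomes and methods of analysis are the same under either number. Most of this stands: it makes 45 the likelier intention and keeps the consequences modest. It does not remove the contradiction, because the document cannot confirm which number was meant. Nor does it help that an article condenses a fuller protocol, since an unseen document cannot make both totals true.

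Two stronger readings are tempting, and the text supports neither.

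- A reader might infer that, in an open-label trial, two totals would let recruitment stop at whichever gives the better result and so inflate the type I error. No section describes an interim look or recruitment that depends on outcomes. Section 2.13 assigns the analysis to a third-party statistician, and section 2.14 assigns data management to a separate department. Participants knowing their group does not mean that pooled results are examined during recruitment.
- A reader might infer that 54 are randomised so that 45 remain evaluable. As the working shows, that requires a loss rate the article does not give and a meaning of 45 that it does not use.

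**Conclusion.** The trial size is wrong as written in at least one place. Section 2.1 conflicts with the abstract and sections 2.5 and 2.11 by 9 participants (3 per arm, 20% of 45), and nothing in the current text reconciles them. The contradiction itself rests on no assumption; it is read directly from four statements about the same quantity. The precision figures, about 0.75 SD against 0.68 SD, assume a two-sided 95% interval, a common SD and complete data, and they illustrate a modest effect. The conclusion does not extend to error rates, and whether 45 is an adequate number for this pilot is not judged here.

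**What to change.** State one randomised total and one per-arm number, identically, in the abstract and in sections 2.1, 2.5 and 2.11. By default, change 54 to 45 in section 2.1 and add 15 per arm there. If the sponsor confirms that 54 is the intended number, change the abstract and sections 2.5 and 2.11 to 54 with 18 per arm, and state why the figures differed. A loss allowance should not be written in merely to bridge the two numbers; it belongs there only if one was actually planned.

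The default costs one corrected number in one section. The alternative costs edits in three places and a sentence of explanation. Neither changes the design or the analysis methods.
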